## Abstract

**Background:**

Dysarthria is a motor speech disorder caused by various neurological diseases, particularly stroke. Individuals with post-stroke dysarthria experience impaired speech intelligibility, communication difficulties, and a reduced quality of life. However, studies on the treatment of post-stroke dysarthria are lacking. Digital speech therapy applications have the advantages of being personalized and easily accessible. However, evidence for their efficacy is not rigorous. Moreover, no studies have investigated both the acute to subacute, and chronic phases of stroke. This study aims to investigate the efficacy and feasibility of digital speech therapy applications in addressing these gaps in dysarthria treatment.

**Methods and design:**

This study is a multicenter, prospective, randomized, evaluator-blinded non-inferiority trial. We aim to recruit 76 participants with post-stroke dysarthria. Eligible participants will be stratified based on the onset period of stroke into acute to subacute, and chronic phases. Participants will be randomized in a 1:1 to receive either a personalized digital speech therapy application or conventional therapy with a workbook for 60 min daily, 5 days a week, for 4 weeks. The primary outcome is the improvement in speech intelligibility. This will be measured by how accurately independent listeners can transcribe passages read by the participants. Secondary outcomes, which include speech function, will be evaluated remotely by speech-language pathologists. This includes the maximum phonation time, oral diadochokinetic rate, and percentage of consonants correct. Participants’ psychological well-being will also be assessed using self-report questionnaires, such as depressive symptoms (Patient Health Questionnaire-9) and quality of life (Quality of Life in the Dysarthric Speaker scale). The trial will also assess the feasibility, participant adherence, and usability of the application. Rigorous data collection and monitoring will be implemented to ensure patient safety.

**Conclusion:**

This trial aims to investigate the efficacy and feasibility of digital speech therapy applications for treating post-stroke dysarthria. The results could establish foundational evidence for future clinical trials with larger sample sizes.

**Clinical trial registration:**

Clinicaltrials.gov, identifier: NCT05865106.

## Introduction

1

Stroke is a leading cause of mortality and long-term disability (1). Stroke can elicit a range of neurological deficits or handicaps, including speech and language problems. Dysarthria is a neurologic motor speech disorder caused by disruptions in the cranial nerve and muscular control of the speech mechanism. It is estimated that approximately 22–60% of stroke patients experience dysarthria within the first week following a stroke (2–4). Approximately 35% of patients continue to exhibit dysarthria even after 6 months (5). Moreover, post-stroke dysarthria significantly impairs speech intelligibility and articulation movements (2). This impairment leads to substantial communication difficulties, emotional distress, social isolation, and poor quality of life (6, 7).

Interventions for dysarthria involve a range of strategies, such as neurorehabilitation, behavioral exercises, and social support (2). Behavioral speech exercises strengthen the breathing and oral muscles to improve speech control. Strategies such as slowing down speech or controlling pitch are also used to enhance speech intelligibility. The treatment plan should be personalized based on the patient’s prior communication ability, recovery stage, and needs (8).

Despite the critical need for effective treatment of dysarthria, traditional therapies are often limited by their monotonous repeated nature. Consequently, these challenges can result in reduced treatment adherence (9). Moreover, the significant time and effort required by physicians and speech-language pathologists (SLPs), often restricts patient access to necessary therapeutic resources (10). Studies have indicated that only approximately one-third of patients receive adequate speech therapy, with substantial variations in therapy frequency (11). Given these limitations, personalized dysarthria treatment becomes necessary because of the diverse patterns of speech impairment in post-stroke dysarthria caused by different stroke lesions (12). These observations highlight the urgent need for alternative approaches, such as personalized digital speech therapy.

Compared with traditional in-clinic methods, these digital applications offer substantial benefits. These include the ability for patients to engage in various speech exercises from home. They improve treatment precision, enhance economic efficiency, ensure patient safety, maintain continuity of care, and support self-management (13, 14). This approach reduces the need for clinic visits and related expenses (15, 16). Furthermore, digital therapy is especially beneficial during the COVID-19 pandemic or endemic as it allows patients to continue their therapy without interruption (17).

Additionally, there is a noticeable lack of high-quality, comprehensive research on the treatment of post-stroke dysarthria. Many existing randomized controlled trials on post-stroke dysarthria have been on a small scale, limiting their ability to provide conclusive evidence regarding the effectiveness of various treatments (18). This significant research gap highlights the importance of our study, which aims to investigate both the efficacy and feasibility of a personalized digital speech therapy application for participants with post-stroke dysarthria.

This study aims to investigate the efficacy and feasibility of a digital speech therapy application for patients with post-stroke dysarthria. Ultimately, our trial seeks to establish our digital speech therapy application as a comprehensive solution. Our application strives to enhance the accessibility and practicality of post-stroke dysarthria. It provides personalized treatments tailored to each patient’s unique needs, thereby overcoming the limitations of traditional rehabilitation methods (12). We hypothesize that our digital speech therapy application would be non-inferior to conventional speech therapies in enhancing patient speech intelligibility and function for post-stroke dysarthria. Additionally, we anticipate positive impacts of our digital speech therapy application on psychological well-being, such as reduced depression and improved quality of life in patients with post-stroke dysarthria. Furthermore, this trial will assess the feasibility of this innovative approach in a clinical setting. It will focus on critical aspects such as recruitment and retention rates, participant adherence, safety, and gathering user feedback.

## Methods and analysis

2

### Trial design

2.1

This study is a multicenter, prospective, randomized, evaluator-blinded, non-inferiority trial designed to evaluate the efficacy and feasibility of a digital speech therapy application for post-stroke dysarthria (Figure 1). Participants will be recruited from three stroke centers in South Korea: Ewha Womans University Seoul Hospital, Mokdong Hospital, and National Rehabilitation Center. The trial will be conducted in accordance with the Declaration of Helsinki (19) and received ethics approval from the Institutional Review Board (Approval number: EUMC 2023–02-002, and NRC-2023-01-007). It is registered on clinicaltrials.gov as NCT05865106.

**Figure 1 fig1:**
[figure not shown]
Study design.

Participants will be recruited based on eligibility criteria (Table 1). Prior to enrollment, participants will receive a detailed explanation of the trial. Following this, written informed consent will be obtained from all participants. Subsequently, the participants’ demographic information and medical histories will be collected. Next, the participants will be randomly assigned to either the intervention or the control group. Randomization will be stratified based on the acute to subacute, and chronic phases of stroke.

**Table 1 tab1:** Inclusion and exclusion criteria.

Inclusion criteria	Justification for inclusion criteria
Aged 18 or over	To maximize the recruitment pool, our age inclusion criterion is set for individuals over 18 years old. However, given the nature of stroke and its higher prevalence in older populations, the majority of our participants are expected to be likely 50 years old or older.
Neurologically stable stroke patients diagnosed by a stroke specialist neurologist and demonstrate no changes in their total National Institute of Health Stroke Scale over 72 h.	Neurologically stable stroke patients suitable for clinical trials can be determined by a clinician to ensure reliable and safe participation during clinical trial.
First-ever stroke patients without previous stroke history.	The efficacy of a digital speech therapy application is hard to confirm for dysarthria caused by pre-existing stroke sequelae.
Paticipants with sufficient cognitive abilities to operate the digital speech therapy application [Korean Mini-Mental State Exam score ≥ 26 (20)].	Cognitive ability can directly influence the patient’s speech improvements and confound results.
As judged by the stroke specialists: participants with sufficient vision [visual acuity and visual field test (21)], hearing [Weber test and Rinne test (22)], communication skills, and motor skills to participate in this study.	Stroke specialists will evaluate potential participants for sufficient vision, hearing, communication, and motor skills. This evaluation will ensure that participants have the necessary abilities to use the digital speech therapy application without difficulty.

Exclusion criteria	Justification for exclusion criteria
Co-existing language disorder (e.g., aphasia). Aphasia will be determined by a stroke specialist using the National Institute of Health Stroke Scale (including fluency, comprehension, repetition, and naming test).	Co-existing language disorders could hinder study participation and cause confounding results.
Co-existing progressive neurological disorders that can affect dysarthria (e.g., dementia, Pick’s disease, Huntington’s disease, Parkinson’s disease, or Parkinsonism).	A major medical comorbidity, including cognitive dysfunction, could interfere with appropriate and reliable performance of intervention or cause confounding results.
Diagnosis of severe mental disorders as determined by a clinician (e.g., schizophrenia, alcohol addiction, or drug addiction).	In order to reliably utilize the application, it is necessary to exclude those with severe mental illness, as determined by the clinician. Mental disorders will be assessed according to participants’ history and current taking medications such as antipsychotics.
Participants taking concomitant medications that could affect the trial results during the study period (e.g., cognitive dysfunction medications, anticholinergics, anti-epileptic drugs, anti-anxiety drugs, antidepressants, antipsychotics, and hypnotics).	Medications that can affect cognitive or emotional function could cause confounding results. However, it is permitted if continued use has been at a stable dose for 2 months prior to randomization in the case of anti-anxiety drugs, antidepressants, and hypnotics.
Participants unable to use/access smartphone technology according to our digital speech therapy application protocol.	The intervention will be provided through the participant’s smartphone application.
Illiterate patients.	Participants must be able to read and understand the intervention delivered by the application.
Participants unable to communicate in Korean.	The application will only be available in Korean language.

### Inclusion procedure

2.2

The principal investigator will screen and exclude participants with abnormalities in oral structures based on speech assessments. A comprehensive list of eligibility criteria is presented in Table 1. Stroke specialists will identify participants with dysarthria using the National Institute of Health Stroke Scale (NIHSS) criteria (23). The NIHSS is utilized for its ease of administration and standardized approach, which minimizes interpersonal variation in assessments. Also, the sub-section of “10. speech” is suitable for initially identifying dysarthria severity in stroke patients. We aim to recruit participants with both mild-to-moderate and severe dysarthria. Mild-to-moderate dysarthria is characterized by slurred speech that remains understandable, and severe dysarthria involves mostly unintelligible speech or the inability to speak without evidence of aphasia. The eligible participants will be referred to a research coordinator to verify their suitability for the trial. To educate the participants, the principal investigator will provide detailed information about the study, such as intervention options, associated risks, and expected benefits. All recruitment and screening processes will be thoroughly documented.

Participants will be clearly informed that they have the right to withdraw from the study at any point without any consequences to their future medical care. Withdrawal criteria will include voluntary withdrawal by the participant, a usage rate falling below 40%, a need for immediate medical care that precludes continued participation, and any adverse events that are directly related to the digital therapy application. Additionally, the research team reserves the right to withdraw participants if there is significant noncompliance with the study protocol or if their health status changes to the extent that continued use of the application is deemed unsuitable or unsafe.

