Maintaining adherence and continuing to participate in the study is a crucial goal. Researchers will systematically offer direct feedback to participants regarding their performance and adherence. This approach encourages continuous patient engagement throughout the therapeutic process. To maintain patient adherence, the researchers will monitor the daily progress of each patient. Researchers will contact participants whenever a decrease in the usage of the application is observed. They will reach out through text messages or phone calls to understand the reasons behind the reduction in their usage. The researchers will then provide encouragement and support to reengage participants in the therapy process. Additionally, the application features daily and monthly calendars for visual progress tracking. It also records the duration of daily activities, fostering motivation and consistency among the participants. Moreover, the participants are encouraged to contact the research team for assistance with application usage challenges, including user errors and interface navigation. Researchers will promptly respond to concerns communicated via phone, email, or text to offer immediate support in resolving issues.

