#### Control group

2.5.2

Participants allocated to the control group will undergo conventional therapy for post-stroke dysarthria over 4 weeks. In the absence of a standard protocol for post-stroke dysarthria treatment in South Korea, we have developed a conventional speech therapy workbook. This workbook integrates various clinically validated behavioral therapy techniques (2, 34). Its content is aligned with the intervention group’s digital speech therapy application to ensure consistency in treatment approaches. Participants will engage in the workbook for 60 min daily, 5 days a week, for 4 weeks to match the intervention group’s treatment dose and frequency. The workbook ensures treatment consistency across the multiple centers involved in this clinical trial. Before starting therapy, the researchers will guide the participants using the conventional therapy workbook.

In line with the intervention group, occasional guidance or support from family members will be allowed. This approach ensures that both groups have access to similar levels of support. By doing so, we promote equality in the treatment conditions across the groups. During regular follow-ups, researchers will monitor the extent and nature of any assistance family members provide. This monitoring will help ensure that the level of support remains balanced and appropriate for both groups.

Researchers will conduct daily follow ups to ensure adherence to conventional therapy workbook. During these interactions, researchers will discuss the participants’ progress, address challenges, and provide support and encouragement to maintain consistent participation in therapy. This approach ensures that the control group receives the same level of attention and support as the intervention group, thereby maintaining trial integrity. After the clinical trial, participants in the control group will also have access to the digital speech therapy application.

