#### Feasibility

2.6.2

A comprehensive evaluation will be conducted to assess the feasibility of this trial. First, the trial will estimate the number of potential participants, the duration of recruitment, and the success rate of screening to secure a representative sample size. Additionally, retention rates will be monitored throughout the trial. These measurements will ensure a rigorous sample size for future studies. Second, the participants’ adherence to digital therapy applications will be measured. This will include tracking the frequency and completeness of the application usage and participant engagement with the treatment protocol using a robust data collection and management system. Third, participant feedback will be collected to assess the acceptability and effectiveness of the digital therapy. We will use the System Usability Scale (SUS) questionnaire to measure the usability of the digital speech therapy application in terms of efficiency and user satisfaction (44). Additionally, interviews will be conducted with the application user to collect qualitative insights such as participants’ experiences, challenges, and suggestions for improvement. This comprehensive feedback will aid in a better understanding of the application’s usability and effectiveness and contribute to future development and enhancements. Finally, we will monitor patient safety and potential adverse events and uphold ethical standards. Digital speech therapy applications include the real-time monitoring of patient log data to swiftly identify and address usage errors or technical issues. Rigorous testing of the application’s performance will also focus on stability and user interface to assess its impact on therapy effectiveness and user experience. This approach ensures the safety and reliability of the digital tools throughout the study.

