### Analysis

2.7

The primary objective of this trial is to investigate the non-inferiority of the intervention group compared to the control group in terms of changes in speech intelligibility from baseline to post-treatment. The hypothesis is as follows:

$$H_{0}:\mu_{t}-\mu_{c}<\delta \;vs\;H_{1}:\mu_{t}-\mu_{c}\geq \delta$$

Where *μt* is the mean change in speech intelligibility score in the intervention group using the digital speech therapy application, and *μc* is the mean change in the control group receiving conventional speech therapy. It is assumed that there is no difference between the two groups, and this study seeks to establish the non-inferiority of the groups. The non-inferiority margin *δ* is set at 19 points, based on the assumption that a difference of 1 to 19 points on the speech intelligibility scale is clinically non-inferior (45).

The sample size required for the non-inferiority trial was determined using a statistical formula (46). This involved setting the significance level (alpha) to 0.025 for a one-sided test and targeting a power of 80% (*β* = 0.2) (47) with a standard deviation of 24.9 (48). This calculation revealed that 28 participants are required for each group. A total of 56 participants are required for the trial. To account for a possible dropout rate of 30%, we aim to recruit a total of 76 participants, with 38 participants in each group.

$$n=\frac{2{\left(z_{\alpha }+z_{\beta }\right)}^{2}\sigma^{2}}{{\left(\mu_{t}-\mu_{c}-\delta \right)}^{2}}\approx 28$$

Analyses will be performed using SPSS software (version 27; IBM Corp., Armonk, New York). Descriptive statistics will summarize the demographic data and outcome measures. For interval estimates, 95% confidence intervals will be provided. An intention-to-treat (ITT) analysis will include all randomized participants. Additionally, we will conduct a per-protocol (PP) analysis which includes only participants who fully adhered to the intended protocol.

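### Withdrawal from the study for low usage or application-related harm falls mainly on the app arm and would leave the ITT analysis resting on imputed week-4 outcomes for those participants

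*Protocol article*

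**What the plan says.** **Withdrawal (2.2 Inclusion procedure).** The paragraph opens by telling participants that "they have the right to withdraw from the study at any point". It then lists the withdrawal criteria: voluntary withdrawal, followed by "a usage rate falling below 40%, a need for immediate medical care that precludes continued participation, and any adverse events that are directly related", the last of these meaning events tied to the app. It adds a discretionary clause: "the research team reserves the right to withdraw participants if there is significant noncompliance with the study protocol", or if a change in health makes further use of the application unsuitable.

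**Usage and adherence by arm.** In 2.5.1 (Intervention group), usage means use of the app: "Researchers will contact participants whenever a decrease in the usage of the application is observed". In 2.5.2 (Control group), adherence is followed by contact: "Researchers will conduct daily follow ups to ensure adherence to conventional therapy workbook". No usage rate or threshold is given for the workbook, and controls receive the app as therapy only after the trial.

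**Outcome timing (2.6 and Table 2).** Speech intelligibility is assessed at baseline and at 4 weeks only.

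**Analysis (2.7).** "An intention-to-treat (ITT) analysis will include all randomized participants". A per-protocol analysis is added, "which includes only participants who fully adhered to the intended protocol". Missing data are to be handled by multiple imputation and LOCF.

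**Feasibility (2.6.2).** Retention is monitored, and "adherence to digital therapy applications will be measured".

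**The concern.** Withdrawal is triggered by events after randomization, namely poor use of the treatment and harm attributed to it, and both triggers are worded around one of the two treatments. If withdrawal ends follow-up, the primary outcome goes missing for reasons tied to how well the app works for that person, and it does so unequally by arm.

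This matters more in a non-inferiority trial than in a superiority trial. Poor uptake is one way in which an unsupervised app could be worse than the workbook, and an ITT comparison should count it. The Discussion itself expects the mechanism: it warns that lack of direct supervision could raise dropout and that older participants may adhere less to digital treatment. If outcomes in low users are replaced by values modelled on those who kept using the app, part of any deficit disappears from the estimate.

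**Working it through.** **1. The plan's own figure.** Inputs from 2.7: one-sided alpha 0.025, power 80%, SD 24.9, margin 19, true difference 0.

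n = 2 × (1.960 + 0.842)² × 24.9² / 19² = 26.96, so 27 per group. The stated 28 is within rounding practice: a noncentral-t calculation gives 80.1% power at 28 per group.

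The plan recruits 38 per arm and allows for 30% dropout. 38 × 0.70 = 26.6, and power at 26–27 per arm is about 77–79% (t-based). Lost power is therefore minor; the issue is bias.

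**2. Who is reached by the criteria.**

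| Criterion in 2.2 | App arm | Workbook arm |
|---|---|---|
| Usage rate below 40% | Yes; usage is monitored daily | No usage rate or threshold stated |
| Adverse event directly related to the app | Yes | Hardly; the app is used only for assessments |
| Urgent medical care | Yes | Yes |
| Significant noncompliance (discretionary) | Yes | Yes, without a cut-off |

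**3. Bias if withdrawn participants are treated like completers.** Let w be the share of the app arm withdrawn under these rules (none in the control arm) and D the amount by which their true 4-week change falls below that of app completers. The app mean is then overstated by w × D. Neither w nor D is in the documents; the ranges are assumptions.

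- w = 0.15, D = 10: 1.5 points (1.5/19 = 8% of the margin)
- w = 0.15, D = 20, or w = 0.30, D = 10: 3 points (16%)
- w = 0.30, D = 20: 6 points (32%)

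**4. Effect on the error rate.** Take a true app-minus-control difference of −19 (the edge of the margin) and 38 randomized per arm. By normal approximation, with SE = 24.9 × √(1/[38(1 − w)] + 1/38), type I error = 1 − Φ(1.960 − wD/SE).

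- w = 0.15, D = 10: SE = 24.9 × √(1/32.3 + 1/38) = 5.96; 1 − Φ(1.960 − 0.252) = 4.4%
- w = 0.30, D = 10: SE = 24.9 × √(1/26.6 + 1/38) = 6.29; 1 − Φ(1.960 − 0.477) = 6.9%
- w = 0.30, D = 20: SE = 6.29; 1 − Φ(1.960 − 0.953) = 15.7%

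Nominal is 2.5%.

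**5. Bias under LOCF.** With one post-baseline visit, LOCF carries the baseline value forward, so the change is 0. If app completers gain G on average, the true app mean is G − wD and LOCF gives (1 − w)G, a bias of w(D − G). With w = 0.30 and D and G each between 10 and 20 (assumed):

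- D = 10, G = 20: 0.30 × (10 − 20) = −3 points (against the app)
- D = 20, G = 10: 0.30 × (20 − 10) = +3 points (in favour of the app)

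If 30% are withdrawn in both arms, withdrawn and retained participants respond alike, and the true difference is −19, LOCF estimates 0.70 × (−19) = −13.3, which is toward non-inferiority. The sign is not fixed in advance.

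**The case against.** **The loss of week-4 data is inferred.** The article never says that assessments stop at withdrawal, and one clause of 2.2 speaks of continued use of the app, which is treatment language. A full protocol may say more. This stands as a limit on certainty. It does not remove the point: the paragraph is about withdrawing from the study, and a site following it as written would have no reason to bring the participant back at week 4.

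**The asymmetry is partly a reading.** The usage rate is undefined, so its application to the workbook cannot be excluded, and the noncompliance clause covers both arms. That is why the point says mainly, not only, the app arm.

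**Stronger readings that the text does not support.**

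- A reader might infer that the rule defeats the ITT analysis. It does not: all randomized participants stay in the set. The weakness is that some results would be imputed when they could be observed.
- A reader might infer that the rule necessarily favours the app. LOCF zeros can penalise it, and the 1.5–6 points apply only where withdrawn participants are treated like completers.
- A reader might take full adherence to exclude anyone who missed a single session and conclude that the per-protocol analysis is badly underpowered. The article does not define the term so, and any power figure would need an assumed adherent fraction that no document gives.
- A reader might say that the rule spoils the feasibility outcomes. A withdrawal for low usage is itself a recorded retention and adherence event.

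**The assumed sizes may be high.** The 30% upper end assigns the whole planned dropout allowance to these rules in one arm, and a 20-point deficit exceeds the margin. Daily monitoring and the requirement for smartphone and cognitive ability make low usage less likely. This is fair; the figures show a range, not a forecast.

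**Conclusion.** The point holds as a conflict between the withdrawal rule in 2.2 and the ITT analysis in 2.7. Followed as written, the rule makes primary outcomes missing for reasons related to adherence and tolerability, mostly in the app arm, and the planned methods for missing data do not reliably repair that.

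The size cannot be read from the documents. On the assumed ranges, completer-like imputation overstates the app by 8–32% of the margin and raises the one-sided error from 2.5% to between 4.4% and 15.7%; LOCF moves the estimate by up to 3 points in either direction. Two inferences carry the conclusion: that withdrawal from the study ends outcome collection, and that the usage rate means app usage. Both follow the article's own wording, but neither is explicit. The matter should be settled while participants are still in follow-up, because week-4 outcomes not collected cannot be recovered at analysis.

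**What to change.** Reconcile 2.2 with 2.7 by separating the end of therapy from the end of outcome collection:

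- Whatever the clinical reason for stopping therapy, collect the scheduled week-4 recording and questionnaires in both arms unless the participant withdraws consent. Record the reason when they cannot be obtained.
- Analyse these data as observed under ITT, so that imputation is needed only for outcomes that are truly missing.
- Measure adherence alike in both arms, and state what the usage rate means for the workbook.
- Handle low adherence through the definition of the per-protocol set, not by ending follow-up.

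Nothing here changes, or takes a view on, when therapy should stop.

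**Cost.** A short amendment and a note to sites, plus a few extra contacts. The recordings are already scheduled and are scored remotely. The app estimate may become less favourable once low users are observed.
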